### Sample size calculation

2.6

For our primary outcome of ulcer recurrence, we estimate 8% recurrence in 12 months in the intervention group. This is a slightly conservative estimate, given the 11% ulcer recurrence in 53 subjects during 93 weeks of follow-up following needle tenotomy as reported by Hedegaard Andersen and colleagues [20]. In the control group, we estimate 36% ulcer recurrence in 12 months. This is slightly more positive compared to the 40% ulcer recurrence in 12 months seen in a recent review [10], and similar to the ulcer recurrence in the control group of a recently completed RCT by these authors [35]. With 8% ulcer recurrence in the intervention group and 36% in the control group, power 0.8, alpha 0.05, 1:1 randomization and intention-to-treat analysis, a total of 66 participants (33 per group) are required.

For our predefined secondary outcome of barefoot peak pressure, we estimate average barefoot peak pressure at the target toe of 400 kPa (standard deviation (SD): 250) in the control group and 180 kPa (SD: 100) in the intervention group following tenotomy. These estimates are based on clinical pilot data from our gait lab, with slightly more conservative estimates than found in our pilot study. With power 0.8, alpha 0.05, 1:1 randomization and intention-to-treat analysis, a total 40 participants (20 per group) are required for this predefined secondary outcome. With this number smaller than required for our primary outcome, the RCT can also be considered adequately powered for this outcome. The calculations were performed using clincalc.com [36].

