### Trial design

2.2

This study concerns a randomized controlled trial (RCT) with a 24-month follow-up period at the out-patient clinic (Table 1). Sixty-six participants will be included. Inclusion started in March 2022. After informed consent is signed, participants are randomized into two groups: usual care (control) or usual care plus flexor tenotomy (intervention). The researchers analyzing the effect of the data will be blinded for group allocation. The treating physician, orthopedic surgeon and participant will not be blinded to group allocation. The flexor tenotomy will be an addition to usual care and is scheduled after randomization. This means that the intervention group will receive the same standard care as the control group including orthopedic shoes.

**Table 1 tbl1:** Standard protocol items.

**Time point**	Study period						
	Enrolment	Allocation	Post-allocation				Close-out
	−2 weeks	−1 week	0	1 week	6 months	12 months	24 months
Enrolment							
Initial eligibility screen	X						
Study information to participant	X						
Initial willingness to participate		X					
Crosscheck inclusion/exclusion criteria		X					
Informed consent			X				
Final eligibility screen			X				
Allocation			X				

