### Statistical analysis

2.7

Statistical analysis will be performed using SPSS. The Shapiro-Wilk W test will be used to determine the distribution. Continuous variables will be expressed as mean ± SD for normally distributed data and as median and interquartile range for not normally distributed and ordinal data. Shapiro-Wilk test and visual inspection will be performed to check for normality. In case of small sample sizes and when data is not normally distributed, Wilcoxon signed rank test will be used. Differences between groups will be compared using Fisher's Exact test or Kruskal-Wallis. A level of p < 0.05 is considered statistically significant.

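### The stated power of 0.8 with 33 per group does not hold for Fisher's exact test: on the same 12-month rates that test has 73% power

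*Protocol article*

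**What the plan says.** Section 2.6 (Sample size calculation) sets the two risks: "we estimate 8% recurrence in 12 months in the intervention group" and "In the control group, we estimate 36% ulcer recurrence in 12 months". From these it concludes: "power 0.8, alpha 0.05, 1:1 randomization and intention-to-treat analysis, a total of 66 participants (33 per group) are required". It names no test, sidedness or formula, only the tool: "The calculations were performed using clincalc.com".

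Section 2.7 (Statistical analysis) gives the between-group tests in one sentence: "Differences between groups will be compared using Fisher's Exact test or Kruskal-Wallis". The significance rule is "A level of p < 0.05 is considered statistically significant".

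Section 2.2 (Trial design) states "Sixty-six participants will be included", which is exactly the number that section 2.6 calls required. It also says: "This study concerns a randomized controlled trial (RCT) with a 24-month follow-up period at the out-patient clinic". Section 2.5.1 defines the main outcome as recurrence on the treated toe over two years.

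**The concern.** A sample size is justified only for the test that will be used. Ulcer recurrence is a yes/no outcome in two groups. Of the two between-group tests named, Fisher's exact test fits such data, while Kruskal-Wallis is for ordinal or continuous data. Fisher's test conditions on the total number of events, so with about 33 per group its true type I error falls well below the nominal 5%, and power falls with it. A formula based on the uncorrected normal approximation does not allow for this.

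If the calculation and the test do not match, the protocol claims more power than its named test delivers on the rates it assumes. A reader of a non-significant result would then credit the trial with more sensitivity, at those rates, than it had. Recruiting exactly the required number leaves no reserve to absorb the difference.

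**Working it through.** **Inputs.** From section 2.6: p1 = 0.08, p2 = 0.36, alpha 0.05, power 0.8, 1:1 allocation, 33 per group. From section 2.7: Fisher's exact test, rejecting at p < 0.05. Two-sided testing is assumed, because the document does not state sidedness.

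**Step 1: reproduce the stated figure.** The uncorrected two-proportion formula with pooled variance under the null is

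n = [z(0.975)·√(2·p̄·(1−p̄)) + z(0.80)·√(p1(1−p1) + p2(1−p2))]² / (p2−p1)²

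- p̄ = (0.08 + 0.36)/2 = 0.22, so 2 × 0.22 × 0.78 = 0.3432, with square root 0.5858.
- p1(1−p1) + p2(1−p2) = 0.0736 + 0.2304 = 0.3040, with square root 0.5514.
- n = (1.960 × 0.5858 + 0.8416 × 0.5514)² / 0.28² = 1.6122² / 0.0784 ≈ 33.15.

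This agrees with the stated 33. Approximate power at 33 per group is 0.798, so rounding down is immaterial. Other two-sided formulas fit less well: 40 per group with continuity correction, 30.4 with unpooled variance and 30.8 with the arcsine transformation.

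**Step 2: exact power of Fisher's test.** Sum the probability of every pair of event counts (i, j) for which Fisher's two-sided p is below 0.05:

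power = Σ Bin(i; n, 0.08) · Bin(j; n, 0.36) · 1[p_Fisher(i, j) < 0.05]

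| n per group | Fisher power, 8% vs 36% |
|---|---|
| 26 | 0.598 |
| 28 | 0.626 |
| 30 | 0.675 |
| 33 | **0.730** |
| 37 | 0.797 |
| 38 | 0.811 |

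At 33 per group the shortfall against 0.80 is 7 points. The target is reached at 38 per group, or 76 in total. The rows at 30, 28 and 26 correspond to assumed losses of about 10%, 15% and 20% (33 × 0.90 = 29.7; 33 × 0.85 = 28.05; 33 × 0.80 = 26.4). The protocol gives no loss rate.

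**Step 3: why the power falls.** With both risks set to the pooled 22%, the same sum gives a true type I error of 0.024 at 33 per group, about half the nominal level.

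**Step 4: alternatives at 33 per group.**

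| Test | Power, 8% vs 36% | Type I error |
|---|---|---|
| Fisher's exact | 0.730 | 0.024 at 22% risk |
| Boschloo's exact | 0.798 | at most 0.05 |
| N−1 chi-square | 0.815 | maximum about 0.057 |

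**Step 5: the 24-month horizon.** If each year's risk repeated in the second year (an assumption), the 24-month risks would be 1 − 0.92² = 15.4% and 1 − 0.64² = 59.0%. Fisher power would then be 0.953 at 33 per group, 0.925 at 30, 0.910 at 28 and 0.887 at 26. With 15.4% against an assumed 50% it would be 0.81 at 33 per group, and against an assumed 45% it would be 0.67.

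**The case against.** The strongest objection is the time horizon. The main outcome covers two years, whereas 8% and 36% are 12-month risks, so 73% is the power of a comparison that is not the primary one. A reader might infer from it that the trial is underpowered for its main outcome, or that true power is 73% or less. The documents do not support that. They give no 24-month rates, and under constant yearly risks Fisher power would be about 95%. This objection stands and limits the point to the calculation as stated. It does not rescue that calculation, which is the only power justification given for the primary outcome.

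Second, the link to Fisher's test and the formula behind 33 are both inferred. Section 2.7 speaks of between-group differences in general and section 2.6 names only a calculator. A fuller protocol or analysis plan may name another primary test. The inference is still sound on the text: no other named test fits a binary comparison, and the 73% follows from the two rates, n = 33 and Fisher's test, whatever formula produced 33. A one-sided reading would remove the gap (one-sided Fisher power 0.823), but nothing in the document points to one-sided testing.

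Third, no loss rate is stated, and handling of missing outcomes is commonly left to the analysis plan. This stands: the figures below 33 per group only illustrate the effect, and the 73% does not rest on them. What the text does show is that 66 are required and 66 will be included.

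Fourth, Fisher's test controls the type I error. That is true: the planned analysis is valid, and only the stated power is affected.

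**Conclusion.** The point holds in limited form. On the protocol's own 12-month rates, with complete follow-up and two-sided testing, the named test that fits the outcome has 73% power at 33 per group, against the stated 80%. Reaching 80% would take 38 per group. Any loss lowers the figure, and the planned recruitment holds no reserve. The conclusion rests on two readings: that Fisher's test applies to the primary comparison and that testing is two-sided. It implies no bias and no excess of false positives, and it says nothing firm about power at 24 months, which depends on rates the protocol does not give. It should be fixed, but it does not threaten the validity of the trial.

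**What to change.** Keep 66 participants and make one of two changes before data are analysed.

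- In section 2.7, name Boschloo's exact test for the binary primary comparison. Power at 33 per group is then 79.8% at the 12-month rates, with size at most 0.05. The cost is one sentence and possibly software beside SPSS.
- Or keep Fisher's exact test and restate the power in section 2.6 as about 73% at the 12-month rates with complete follow-up. The cost is one corrected figure.

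The N−1 chi-square should not be offered as a cost-free substitute, because its maximum size at 33 per group is about 0.057. Neither change creates a reserve for loss, so section 2.6 should also say that its power figure assumes complete follow-up.

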### Statistical analysis

2.7

Statistical analysis will be performed using SPSS. The Shapiro-Wilk W test will be used to determine the distribution. Continuous variables will be expressed as mean ± SD for normally distributed data and as median and interquartile range for not normally distributed and ordinal data. Shapiro-Wilk test and visual inspection will be performed to check for normality. In case of small sample sizes and when data is not normally distributed, Wilcoxon signed rank test will be used. Differences between groups will be compared using Fisher's Exact test or Kruskal-Wallis. A level of p < 0.05 is considered statistically significant.

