#### Cost-effectiveness

2.5.5

With the economic evaluation the total costs related to diabetic foot disease for all participants will be determined. These costs will be related to the effects of the treatments in the groups. The outcomes of the EQ-5D-5L and SF-36 will be used in the economic evaluation to determine cost-utility and the ulcer recurrence is used to determine cost-effectiveness. All relevant costs related to treatment will be recorded. These include.•Cost of the flexor tenotomy•Other costs related to prevention of recurrent ulcers prescribed at the diabetic foot rehabilitation out-patient clinic. These include: orthopedic footwear and adaptations to the footwear, felted foam, casts and orthoses•Costs of treatment of recurrent ulcers or newly formed ulcers: wound dressing, antibiotics and treatment by podiatrist at the diabetic feet rehabilitation out-patient clinic, costs of hospitalization, interventions related to ulceration (amputation) and homecare hired due to foot ulceration•Costs related to additional visits to the podiatrist, general practitioner, emergency department or the diabetic feet rehabilitation out-patient clinic due to diabetic foot ulcers

The costs will be valued using the guidelines published in the updated handbook for economic evaluation in the Netherlands [34]. The costs of medication will be estimated on the basis of prices charged by the Royal Society of Pharmacy.

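### The only between-group rule for continuous outcomes in section 2.7 is rank-based and does not exempt costs; read literally, it does not test the mean cost difference that the economic evaluation needs

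*Protocol article*

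**What the plan says.** Section 2.7 of the protocol article summarizes continuous variables as mean and SD if normally distributed, and otherwise "as median and interquartile range for not normally distributed and ordinal data". For comparing the arms it says: "Differences between groups will be compared using Fisher's Exact test or Kruskal-Wallis". The Wilcoxon signed-rank test, also named there, is a paired test and does not compare arms. No test or interval for a difference in means appears, and no outcome is set apart.

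Cost-effectiveness is a secondary objective (section 2.1), and costs have their own entry under Outcomes (section 2.5.5): "With the economic evaluation the total costs related to diabetic foot disease for all participants will be determined". The next sentence reads: "These costs will be related to the effects of the treatments in the groups". The items include "Cost of the flexor tenotomy", borne by one arm only, and "costs of hospitalization, interventions related to ulceration (amputation) and homecare hired due to foot ulceration". The Dutch handbook is cited for valuation: "The costs will be valued using the guidelines published in the updated handbook for economic evaluation in the Netherlands". Neither section states how costs are compared between arms.

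**The concern.** Total cost is the number of participants times the arithmetic mean, and an incremental ratio divides a mean cost difference by a mean effect difference. The Kruskal-Wallis null is that the two cost distributions are the same. That is a different hypothesis from equal mean cost, and the test gives no estimate of the mean difference.

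The gap matters here because the cost structure differs between arms. Tenotomy shifts the cost of every intervention participant upward. The saving comes from ulcers that do not occur, so it is concentrated in the participants who would otherwise have recurred, some at very high cost. Ranks record the uniform shift in full but cap the weight of each large cost. A report that followed section 2.7 literally could show a significant cost difference where mean costs are equal, or a rank result that disagrees with the mean difference in its own cost-effectiveness ratio.

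**Working it through.** **Inputs from the article.** 33 per arm; recurrence at 12 months p1 = 0.08 (intervention) and p0 = 0.36 (control); alpha 0.05, taken as two-sided; follow-up 24 months.

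**The plan's own figure.** Pooled normal formula without continuity correction, mean proportion 0.22:
n = [1.96 × √(2 × 0.22 × 0.78) + 0.842 × √(0.08 × 0.92 + 0.36 × 0.64)]² / 0.28² = (1.148 + 0.464)² / 0.0784 ≈ 33.2 per arm. Rounded up this is 34 per arm, 68 in total. Power at 33 per arm is 79.8%. The stated 66 is reproduced to within two participants.

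**24-month rates** (assumption: constant yearly risk). Intervention 1 − 0.92² = 0.154; control 1 − 0.64² = 0.590.

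**Cost model** (all prices are assumptions). Preventive-care cost is lognormal with mean 1 unit and coefficient of variation (CV) 0.3 to 1.0. Tenotomy costs x units. Cost per ulcer is lognormal with mean U and CV 1.5.
- Mean cost, intervention: 1 + x + p1·U
- Mean cost, control: 1 + p0·U
- Equal means (break-even): U = x / (p0 − p1). At 12-month rates this is x / 0.28, so U = 0.89, 1.79 and 3.57 for x = 0.25, 0.5 and 1.
- With U at twice break-even, tenotomy saves 2x − x = x per participant; at four times, 3x.

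**Equal mean costs, care-cost CV 0.5, 4,000 trials per scenario: share with p < 0.05**

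| x | Kruskal-Wallis, 12-month rates | Kruskal-Wallis, 24-month rates |
|---|---|---|
| 0.25 | 14% | 8% |
| 0.5 | about 44% | 22% |
| 1 | 81% | 51% |

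Nearly all of these rejections point to tenotomy as dearer. Over care-cost CV 0.3 to 1.0 and x from 0.25 to 1, Kruskal-Wallis rejects in about 9–91% (12-month rates) and 7–64% (24-month rates). A Welch test of means rejects in about 4–9%. At x = 0.1, Kruskal-Wallis rejects in about 5–7%.

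**Tenotomy truly cost-saving: share of trials in which Kruskal-Wallis calls it significantly dearer**
- Twice break-even, 12-month rates, CV 0.5: 5%, 22% and 59% for x = 0.25, 0.5 and 1.
- Twice break-even, 24-month rates, CV 0.5: 1.0%, 3.7% and 10.2%; about 1–15% over the CV range.
- Four times break-even, 24-month rates, CV 0.5: 0.2%, 0.4% and 2.1%; about 0–3% over the CV range. Significant results then mostly point the right way (21%, 12% and 7% cheaper).

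**A second cost model** (usual-care cost 0 to 0.4U, ulcer cost with log-SD 1, 1,500 trials per scenario) gives the same picture. With equal means, Kruskal-Wallis calls tenotomy dearer in 56–91% (12-month rates) and 42–63% (24-month rates), against 5–9% for Welch. With tenotomy priced at half the ulcer cost it avoids, the figures are 8–73% and 2–14%; at a quarter, 1–65% and 0.1–3%. Costs in this model failed Shapiro-Wilk in at least 99.6% of trials, so the median summary would be used. The choice of Kruskal-Wallis does not depend on that step, because section 2.7 names no other between-group test for continuous data.

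**The case against.** The strongest reply is that section 2.7 never mentions costs. Section 2.5.5 describes a separate economic evaluation that relates costs to effects, and a rank test cannot produce cost-utility or cost-effectiveness. The economic estimator may well sit in a full protocol or economic analysis plan that is not shown, and a condensed article may leave it there. This stands in part: a reader might infer that the plan has decided to test costs by Kruskal-Wallis, and the article does not say so. The application follows only from the lack of an exemption. What remains is a stated rule with general wording that, taken literally, answers a different question from section 2.5.5.

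A reader might also infer that the rule is bound to count against tenotomy, or will usually call it dearer when it saves money. The article does not support that. It gives no prices, and the large percentages need tenotomy to cost a sizeable share of a participant's whole preventive care, although the article describes a needle procedure of one to two minutes in the out-patient clinic. Nor can one say that the median participant in both arms stays free of recurrence. That holds at the 12-month rates, but at the extrapolated 24-month rate 59% of controls have recurred. Over the trial's own horizon the reversal is uncommon.

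**Conclusion.** The point holds as a mismatch between the general rule in section 2.7 and the question in section 2.5.5. Read literally, the rule does not test the difference in arithmetic mean cost. With equal means it can reject far more often than 5%, and this persists at 24-month rates unless tenotomy is cheap relative to preventive care. The size rests on assumed prices, on lognormal costs and, for 24 months, on a constant yearly risk of recurrence. A significant result in the wrong direction when tenotomy saves money is a possibility, not an expectation. The same reasoning extends to QALYs if they are skewed, but that was not quantified. A secondary objective is affected; the primary ulcer comparison is not.

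**What to change.** Add a sentence to section 2.7 or 2.5.5 stating that costs and QALYs are exempt from the median and Kruskal-Wallis rule. For both, report arithmetic means per arm and the between-arm mean difference with a non-parametric bootstrap 95% confidence interval, resampling participants within arm and keeping each participant's cost and effect together. Build the incremental ratios from the same bootstrap samples. Medians can be shown as description, without a rank test on costs. If an economic analysis plan already says this, a cross-reference is enough.

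The change needs no new data or participants, only a little analysis work. The drawback is that intervals for mean cost will be wide at 33 per arm.

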## Introduction

1

Diabetic foot ulcers are a common problem, with a global prevalence of 6.3% in people with diabetes, and are one of the biggest risk factors for lower extremity amputation [[1], [2], [3]]. The formation of these ulcers is multifactorial and causes include peripheral neuropathy, vascular deficiency and mechanical stress [4]. In peripheral neuropathy the protective sensation in the extremities, mainly in the feet, deteriorates [5]. Detection of foot trauma is diminished causing people with diabetes to neglect taking measures when risk for foot ulcers increases. Hyperglycemia impairs leukocyte and complement function, thereby increasing chances for invasive infections [6]. Micro- and macrovascular disease is a co-morbidity often seen in people with diabetes mellitus debilitating ulcer healing [7]. Diabetic foot ulcers require off-loading treatment (e.g. total contact casts) often accompanied by (long-term) antibiotics [8]. These treatments can burden people in their daily activities. When healed, these ulcers have a high recurrence rate of 40% per person per year in Europe [9,10]. Prevention of diabetic ulcers is therefore of great importance.

In people with diabetic peripheral polyneuropathy, deformities of the feet are more prevalent than in people without diabetes [11]. Common deformities are claw toe and hammer toe deformity. The exact mechanism behind these deformities in this patient group is not fully understood, but seems related to a mismatch in extensor and flexor function due to intrinsic muscle atrophy [12]. In claw/hammer toe deformity there is additional pressure either underneath the metatarsal heads or on the tip of the toe [13]. This excess pressure increases the chance of ulcer development on these places on the foot. Claw/hammer toe deformity can be treated conventionally with off-loading techniques such as orthopedic shoes or a toe orthosis [11]. This is not always sufficient since pressure points can still occur when the shoes do not fit properly or when the patient is not adherent to wearing them [14].

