**Assessments**							
Demographic and disease-related characteristics			X				
Barefoot pressure			X		X	X	
Weight-bearing CT			X		X	X	
SF-36			X		X	X	X
EQ-5D-5L			X		X	X	X
Ulcer formation			X	X	X	X	X
Notes of received foot care					X	X	X
Process evaluation					X	X	X

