### Eligibility criteria

2.3

In order to be eligible to participate in this study, a participant must meet all of the following criteria.•A minimum age of 18 years•Sufficient understanding of Dutch/English language•Capable of providing informed consent•Loss of protective sensation as a result of peripheral polyneuropathy•Diabetes mellitus type 1 or 2•A minimum of 1 claw/hammer toe on either foot•A documented history of diabetic (pre-)ulcers underneath the tip of the toe in the past 5 years. Pre-ulcers include abnormalities of or damage to the nail, callus formation and hematomas.

A potential participant who meets any of the following criteria will be excluded from participation in this study.•Open ulcer(s) on the toes•Previous participation in the study•Pregnant women•Concomitant participation in a study in which the participant is exposed to X-rays (due to the use of weight-bearing CT in this study)•Critical ischemia (i.e. ankle-brachial index <0.5 or toe pressure <30 mmHg)

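### The one between-group test that fits the binary primary outcome, an unadjusted Fisher's exact test, has about 73% power at the planning rates rather than 80%, and leaves ulcer versus pre-ulcer history unused

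*Protocol article*

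**What the plan says.** - **Test (section 2.7).** "Differences between groups will be compared using Fisher's Exact test or Kruskal-Wallis", and "A level of p < 0.05 is considered statistically significant". No covariate or stratum is named. The main outcome in section 2.5.1 is recurrence on the treated toe within 2 years, which is binary, so Fisher's test is the one that applies.
- **Sample size (section 2.6).** "we estimate 8% recurrence in 12 months in the intervention group"; the control figure is 36%. The result is given as "power 0.8, alpha 0.05, 1:1 randomization and intention-to-treat analysis, a total of 66 participants (33 per group) are required".
- **Entry (section 2.3).** Participants need "A documented history of diabetic (pre-)ulcers underneath the tip of the toe in the past 5 years". Callus, nail damage and hematoma count as pre-ulcers, so people with and without a true ulcer in the past can both enter.
- **Baseline data (Table 1).** The relevant row reads only "Demographic and disease-related characteristics". Ulcer versus pre-ulcer is not listed as a variable of its own.
- **Recurrence rates.** The Introduction says of healed ulcers that "these ulcers have a high recurrence rate of 40% per person per year in Europe". The article gives no rate for people who had only pre-ulcers.
- **Allocation (section 2.2).** Randomisation is to two groups, with no stratification factor described.

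**The concern.** Two things are at stake.

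First, the sample size and the named test do not belong together. Fisher's test is conservative in small trials. A size taken from an uncorrected test of two proportions will not deliver its stated power when Fisher's test is the one applied.

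Second, the trial mixes people with a past toe ulcer and people with only pre-ulcer signs, and these may differ in their risk of recurrence. With 33 per arm and no stratified allocation described, the arms can differ by chance in this mix. Fisher's test on one pooled table cannot take that into account, although the information should be on file for every participant.

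**Working it through.** **Inputs from the article:** risks 0.36 and 0.08, 33 per arm, alpha 0.05 (taken as two-sided), power 0.80. **Assumed, because the article does not give them:** share with a prior ulcer 30% to 70%; odds ratio (OR) of recurrence for prior ulcer versus pre-ulcer only, 1 to 6; overall arm risks held at 36% and 8%.

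**1. The plan's own figure.** Mean risk (0.36 + 0.08)/2 = 0.22.

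n = [1.960 × √(2 × 0.22 × 0.78) + 0.842 × √(0.36 × 0.64 + 0.08 × 0.92)]² / 0.28² = (1.148 + 0.464)² / 0.0784 = 33.2 per arm.

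This reproduces 33 per arm to rounding, and the same formula gives 79.8% power at 33. With a continuity correction the two-sided formula gives 40 per arm, so the plan used an uncorrected two-sided test, or something equivalent to it.

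**2. Power of the named test.** Every possible pair of event counts was enumerated at 33 per arm:
- Fisher's exact: 73.0% power. True type I error is 2.4% at a common risk of 22% and 2.9% at 36%.
- Uncorrected chi-square: 82.6% power. True type I error is 5.2% and 5.6% at the same risks.
- Fisher at 36 per arm gives 78.2%, and at 38 per arm 81.1%.

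**3. Stratifying by history.** Simulated at 33 per arm, 8,000 trials per row (simulation error about 0.5 point), power in %:

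| Prior-ulcer share | OR | Fisher | Chi-square | CMH | Stratified exact | CMH minus chi-square |
|---|---|---|---|---|---|---|
| 30% | 1 | 73.0 | 81.9 | 80.7 | 75.5 | -1.2 |
| 30% | 3 | 73.3 | 82.6 | 82.8 | 77.6 | +0.2 |
| 30% | 6 | 73.4 | 82.8 | 85.9 | 81.0 | +3.0 |
| 50% | 1 | 72.4 | 82.2 | 80.9 | 75.6 | -1.3 |
| 50% | 3 | 73.3 | 82.9 | 83.1 | 78.2 | +0.3 |
| 50% | 6 | 72.8 | 82.6 | 84.9 | 80.3 | +2.3 |
| 70% | 1 | 73.2 | 82.7 | 81.5 | 76.2 | -1.2 |
| 70% | 3 | 73.5 | 82.8 | 82.9 | 77.9 | +0.1 |
| 70% | 6 | 73.0 | 82.1 | 83.3 | 78.5 | +1.2 |

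Both stratified tests beat Fisher in every row. The last column is the part due to history. The rest comes from leaving a very discrete test. In null simulations the type I error of CMH was 4.8% to 5.3%, and that of the stratified exact test 3.2% to 4.1%.

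**4. The two-year outcome.** The planning rates are for 12 months. Under an assumed constant hazard, the 24-month risks are 1 - 0.92² = 15.4% and 1 - 0.64² = 59.0%. Fisher's power is then 95.3%. At a 50% share and OR 1, 3 and 6, CMH gives 97.1%, 97.7% and 98.5%, and the stratified exact test 95.8%, 96.9% and 97.8%. The gain over Fisher is about 0 to 3 points.

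**5. Chance imbalance.** At a 50% share, the difference between two Binomial(33, 0.5) counts is 5 or more in 26.8% of trials. A gap of 5 is 5/33 = 15.2 percentage points.
- OR 3: the stratum risks differ by 24.5 points in controls (23.7% and 48.3%) and by 7.5 in the intervention arm. The shift in the crude risk difference is 0.152 × (24.5 + 7.5)/2 = 2.4 points, or 0.152 × 24.5 = 3.7 at control-arm risks.
- OR 6: the differences are 38.1 and 10.9 points. The shift is 0.152 × (38.1 + 10.9)/2 = 3.7 points, or 5.8 at control-arm risks.

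The standard error of the crude risk difference is √(0.36 × 0.64/33 + 0.08 × 0.92/33) = 9.6 points.

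**6. Room for one factor.** Expected events: 33 × 0.36 + 33 × 0.08 = 14.5. That supports one binary stratum and no more.

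**The case against.** - **The article is condensed.** Section 2.7 is one general paragraph, does not tie Fisher's test to the primary outcome by name, and an analysis plan not shown may contain an adjusted analysis. The lack of an adjustment would not be a finding by itself. This point rests on what is stated: a named test that falls short of the power claimed one section earlier.
- **History is not needed to regain the power.** This stands. An unadjusted, uncorrected chi-square already reaches 82.6%, at a type I error slightly above 5%. A reader might infer that ignoring history is what costs the power; the like-for-like comparison does not support that. Gains of 7 points or more over Fisher from the stratified exact test need an odds ratio near 6, for which the article has no source.
- **The planning rates are not those of the two-year outcome.** This also stands. At 15% versus 59% there is little left to gain. Less favourable rates are possible too: at 15% versus 45%, enumeration gives Fisher about 69%.
- **Imbalance is not bias.** A reader might infer that chance imbalance in history makes the planned result wrong. It does not. Under randomisation Fisher's test keeps its error below 5%, and a shift of 2 to 4 points is about a quarter to two-fifths of one standard error, which the unadjusted inference already reflects.
- **History type may not be captured.** The article requires a documented history but does not list its type as a variable. That it can be recovered from the eligibility record is a reasonable inference and no more.

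**Conclusion.** The point holds as a matter of efficiency and precision. The named test gives about 73% power where the article states 80%, and uses only 2.4% to 2.9% of the 5% error it is allowed. That result needs no assumption beyond the article's own rates and a two-sided test. The main cause is the discreteness of Fisher's test, set against a sample size from an uncorrected test.

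A test stratified by history does better than Fisher in every scenario examined: about 80% to 86% power for CMH and 75% to 82% for the stratified exact test. History itself accounts for about -1 to +3 points of the CMH figure. These ranges rest on assumed shares and odds ratios and on the 12-month rates. The added benefit of stratifying is a better-balanced estimate in a small trial, worth roughly 2 to 4 points on the risk difference when the arms differ by 5 prior-ulcer participants, and up to 4 to 6 points at control-arm risks. The change is worth making because it is cheap; the planned analysis is valid without it.

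**What to change.** In section 2.7:

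1. Name as primary test for ulcer recurrence a CMH test, or an exact conditional test of the common odds ratio, stratified by one binary factor: prior ulcer on the tip of the toe versus pre-ulcer only. CMH has the higher power but is asymptotic; the exact version guarantees the error rate and, in the scenarios above, reaches 80% only near an odds ratio of 6.
2. Report the Mantel-Haenszel risk difference with its 95% CI.
3. Keep the unadjusted Fisher test as a sensitivity analysis.
4. Add history type as an explicit baseline item, completed from the eligibility record without knowledge of outcome.
5. Add no further strata, given about 14.5 expected events.

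**Cost:** a sentence or two in the analysis section and one baseline field. No extra participants or visits are needed, provided history type can be recovered for those already enrolled. The estimate becomes stratum-weighted instead of crude. The choice must be fixed before outcomes are seen by arm.
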